### Publication of data

Data will be published after a follow-up period of 1, 2, and 5 years, regardless of the outcome of the study under the responsibility of dr. [name]. Co-authorship will be assigned according to the ' Uniform Requirements for Manuscripts Submitted to Biomedical Journals: Writing and Editing for Biomedical Publication' of the International Committee of Medical Journal Editors.

### Definitions

• Procedural success:

○ Endovascular - Successful vascular access, exact deployment of the device and completion of the endovascular procedure and immediate morphological effect (< 30% residual stenosis)

○ Surgical - Successful access, completion of surgical procedure and clinically assessed immediate improvement

• Primary patency: The absence of occlusion or flow-limiting stenosis (PSV ratio > 2.5) of the treated segment of the artery including 1 cm proximal and distal of the anastomosis, as documented by accepted imaging techniques, particularly arteriography or duplex ultrasonography, or direct observation at operation or postmortem.

• Primary assisted patency: When a secondary endovascular or open procedure is performed to prevent failure, i.e. in a flow reducing stenosis (PSV ratio > 2.5), in a still-patent segment of the stent graft or bypass, including the anastomoses.

• Secondary patency: When a thrombolytic or surgical treatment has been performed for graft or stent graft occlusion in an afterwards patent vessel.

• Target lesion revascularization: Repeat percutaneous or surgical revascularization driven by clinical state in the presence of a flow reducing stenosis or occlusion in the treated segment of the artery including 1 cm proximal and distal of the anastomosis.

• Type B lesion SFA according to TASC II criteria:

○ Multiple lesions (stenosis or occlusions), each ≤ 5 cm

○ Single stenosis or occlusions ≤ 15 cm (not involving infragenuale popliteal segment)

○ Heavily calcified occlusion ≤ 5 cm in length

○ Single popliteal stenosis

• Type C lesion SFA according to TASC II criteria:

○ Multiple stenosis or occlusions totaling > 15 cm with or without heavy calcification

○ Recurrent stenosis or occlusions that need treatment after 2 endovascular interventions

• Type D lesion SFA according to TASC II criteria:

○ Chronic total occlusions of CFA or SFA (> 20 cm, involving the popliteal artery)

○ Chronic total occlusions of popliteal artery and proximal trifurcation arteries

• Minor amputation: Below the ankle amputation, planned or unplanned.

• Major amputation: Above the ankle amputation, planned or unplanned

• Clinical improvement: Improved Rutherford classification compared to baseline.

• Intermediate lesion: Occlusion or stenosis > 10 cm length

• Flow-reducing (re-)stenosis: A stenosis with a PSV ratio of more than 2.5 as measured by duplex, or a > 50% (re-)stenosis on angiography, MRA or CTA.

• Graft failure: Definitive occlusion of the bypass with unsuccessful thrombolytic or surgical treatment

• Re-intervention: Secondary percutaneous or surgical intervention of the bypass.

• Seroma - Non-infected fluid accumulation under the wound

• Hematoma - Accumulation of blood postoperatively in the operated area.

• Re-bleed - Accumulation of blood postoperatively requiring operative treatment.

• Abscess - Accumulation of pus in the operated area.

• Infected wound - Red, swollen, but closed wound, not requiring surgical drainage.

• Open wound - Non infected wound leaking fluid.

• Loss of sensibility - Postoperative clinical loss of sensibility of the skin in the operated leg.

• Femoral nerve damage - Clinical femoral nerve damage.

• Graft infection - Proven graft infection requiring long term use of antibiotics or graft removal.

• Edema - Postoperative persistent edema of the operated leg.

• Serious adverse event (SAE): An adverse event that leads to death or serious deterioration in the health of the subject, defined as death, definite failure of graft/bypass or major amputation in the treated leg

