#### Adverse and severe adverse events

Adverse events (AE) are defined as any undesirable experience occurring to a participant during the study, whether or not considered related to the investigational device. This definition includes events occurring during hospital stay up to 30 days of follow-up. Underlying disease that was present at the time of enrollment is not reported as an AE, but any increase in the severity of the underlying disease will be reported as an AE. All AEs will be monitored from the time of enrolment through the 30-day follow-up visit. AEs will be recorded on the case record forms (CRFs). A description of the event, including the start date, end date, action taken, and the outcome will be provided.

A severe adverse event (SAE) is any event leading to death, major amputation or definitive graft failure.

Data on AEs will be reported to the DSMB and to the accredited METC via "Toetsingonline" on the website of the Central Committee on Research involving Human Subjects (CCMO, ccmo.nl).

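### Graft failure requires a failed re-treatment, so on the natural reading a permanent occlusion left untreated is an SAE only if it leads to death or major amputation

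*Protocol article*

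**What the plan says.** The Definitions section of the protocol article has this entry: "Graft failure: Definitive occlusion of the bypass with unsuccessful thrombolytic or surgical treatment". 

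Seriousness is defined twice, each time as a list of three outcomes. The section on adverse and severe adverse events has: "A severe adverse event (SAE) is any event leading to death, major amputation or definitive graft failure". The SAE entry in Definitions has: "defined as death, definite failure of graft/bypass or major amputation in the treated leg". Neither refers to the graft-failure entry, but that is the only place where failure of a graft is defined.

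Three further rules bear on the point:
- Adverse events are defined broadly, "Adverse events (AE) are defined as any undesirable experience occurring to a participant during the study, whether or not considered related to the investigational device", but with a limited window: "All AEs will be monitored from the time of enrolment through the 30-day follow-up visit".
- Patency loss does not depend on treatment: "Primary patency: The absence of occlusion or flow-limiting stenosis (PSV ratio > 2.5) of the treated segment of the artery".
- Secondary patency does depend on it: "When a thrombolytic or surgical treatment has been performed for graft or stent graft occlusion in an afterwards patent vessel".

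**The concern.** Whether a lost graft counts as a failure should depend on the state of the graft. Here it also depends on whether someone tried to reopen it. Two patients with the same permanent occlusion are classified differently if one has an unsuccessful attempt and the other has none.

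The untreated case is plausible in this trial. Eligibility runs from Rutherford 3 to 6, and duplex is scheduled at every follow-up visit to 5 years, so occlusions will be found in patients whose symptoms do not prompt another procedure. The article itself makes target lesion revascularization depend on the patient's clinical state.

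The treating team knows whether the patient had open surgery or an endograft. If the readiness to re-treat differs between arms, recorded graft failures and SAEs could differ for the same number of lost grafts. The Discussion aims to show fewer complications with the endovascular approach, and the DSMB reviews safety, so a count with this dependence could be misread as a difference between devices.

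**Working it through.** **Step 1. The plan's own figures, to see whether they depend on the definition.** Inputs from the sample size section: 90% patency in both arms, margin 10%, alpha 5%, power 80%. Taking alpha as one-sided:

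n = (1.645 + 0.842)² × 2 × 0.9 × 0.1 / 0.10² = 6.18 × 18 = 111.3 per group, against 111 stated (112 if rounded up).

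For quality of life (difference 10, SD 20, two-sided 5%, power 80%):

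n = 2 × (1.960 + 0.842)² × 20² / 10² = 62.8, so 63, as stated.

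Neither formula uses graft failure. Both figures stand whatever is done about the definition.

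**Step 2. The definitions side by side.** Each row is a patient whose bypass or endograft occludes.

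| Course after occlusion | Primary patency | Secondary patency | Graft failure | SAE |
|---|---|---|---|---|
| Thrombolysis or surgery, reopened | lost | yes | no | no |
| Thrombolysis or surgery, unsuccessful | lost | no | yes | yes |
| No attempt; no death or major amputation | lost | no | no | no |
| No attempt; leads to death or major amputation | lost | no | no | yes |
| Percutaneous attempt without thrombolysis, unsuccessful | lost | no | unclear | unclear |

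The third row is the gap. The graft is permanently lost, yet apart from loss of primary patency, which pools occlusion with stenosis, no defined category takes it. Within the AE window it can be recorded as an AE; after that the article gives it no safety category. The last row is unclear because the graft-failure entry names only thrombolytic and surgical treatment, while another entry reads: "Re-intervention: Secondary percutaneous or surgical intervention of the bypass".

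**Step 3. Size, as an illustration only.** The documents give neither an occlusion rate nor the share of occlusions left untreated.
- Patients per arm: 111. Planned 1-year patency: 90% (sample size section, with the endograft assumed similar).
- Losses of patency per arm: 111 × (1 − 0.90) = 11.1.
- Assumption: half are occlusions, 11.1 × 0.5 = 5.6.
- Assumption: 0 to 50% of these are not re-treated, 5.6 × 0 = 0 to 5.6 × 0.5 = 2.8.
- Result: about 0 to 3 per arm outside the definition by 1 year.

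A wider sweep, with occlusion in 5 to 15% and 10 to 50% of occlusions untreated, gives 111 × 0.05 × 0.10 = 0.6 to 111 × 0.15 × 0.50 = 8.3 per arm. Its upper end lies outside the planning assumption, because 15% occlusion alone exceeds a 10% loss of patency.

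**Step 4. The interim safety look.** It is planned one year after initiation on at least 40 patients. With 40 patients and the Step 3 assumptions, 40 × 0.10 × 0.5 × 0.5 = 1.0. That is about one patient over both arms at most, and fewer in practice because most would not yet have a full year of follow-up.

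**The case against.** The strongest reply is that the gap is narrow and lost grafts stay visible. Primary patency is lost with any occlusion, treated or not, and duplex is done at every planned visit. An untreated occlusion cannot pass as secondary patency. Neither graft failure nor an SAE count is named as an endpoint; complications are, but without reference to SAEs. All of this stands, and it confines the point to safety reporting.

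The link to the SAE rule is also inferred. The two SAE texts use slightly different terms and do not cite the graft-failure entry, so an investigator could report an untreated permanent occlusion as a definite failure of the bypass. That is fair. But if the SAE component means something other than the defined term, it has no definition, and sites may apply it differently. The text needs repair on either reading.

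The window matters too. One SAE entry describes an SAE as a kind of adverse event, and AEs are monitored to 30 days. If SAEs share that window, the 1-year illustration overstates the number missed from the SAE count, and the documents give no 30-day occlusion rate. The SAE sentence in the safety section sets no window.

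A reader might infer that an untreated occlusion can never be an SAE. It can, through death or major amputation. A reader might also infer that the DSMB would be falsely reassured. That is not supported: AE data go to the DSMB, so an untreated occlusion recorded as an AE within 30 days reaches it.

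On percutaneous attempts, the secondary-patency entry uses the same pair of treatments as the graft-failure entry, so the pair may be shorthand for any reopening procedure. This part is ambiguity, not clear exclusion.

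**Conclusion.** The point holds as a defect in a stated outcome definition. Read literally, graft failure requires an unsuccessful treatment, and on the natural reading this carries into the SAE count, which then partly reflects the decision to re-treat. The size is uncertain and probably small: about 0 to 3 patients per arm by 1 year, given the planned 90% patency, half of the losses being occlusions, and up to half of those left untreated. The last two are assumptions.

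Larger figures are tempting but should not be used. With the 1-year rates in the Background section, 87% for venous bypass and 73% for a covered stent, losses would be 111 × 0.13 = 14.4 and 111 × 0.27 = 30.0 per arm. The 73%, however, comes from an earlier covered stent without the heparin-bonded technology, and the trial is planned on similar patency in both arms. Nor do the documents say that non-treatment differs by arm, or in which direction. A ratio of recorded failures between arms could only be built from invented rates. That it could differ is enough to justify the change; how far it would is not known.

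**What to change.** Replace the graft-failure entry with one that applies to both arms: occlusion of the bypass or endograft that is not reopened, whether or not re-treatment was attempted and whatever its type (thrombolytic, percutaneous or surgical). Record on the case report form, as a separate item, whether an attempt was made and of what kind, so that the re-treatment decision can be described by arm. Refer both SAE definitions to this single entry, in the same words, and state the period over which SAEs are collected.

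This changes the classification of an outcome and nobody's treatment. The scheduled duplex examinations already detect the occlusions. The cost is one reworded definition, two cross-references, one item on the form and slightly more SAEs to report. Sample size and the primary endpoints stay as they are.

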## Discussion

The aim of the present randomized trial is two-fold. First, it aims to compare patency rates of the endoluminal bypass, combined with the heparin-bonded technology, with the current gold standard, the venous femoro-popliteal bypass, the current gold standard. Second, it aims to demonstrate that an endovascular approach is associated with fewer complications and thus an improved quality of life. In order to have sufficient power, the trial was designed using a non-inferiority principle.

Data analysis will be performed in both an intention-to-treat as a per-protocol manner. The first will be performed to compare the endoluminal bypass with common surgical practice, namely that some patients will not have a vein usable for the bypass and that some endoluminal procedures will be converted to open surgery. The per-protocol analysis will give information about the performance of the endoluminal bypass itself.

There are several differences between the SuperB trial and previously published randomized trials [9,16]. The SuperB trial is the first trial using a heparin-bonded endograft and the inclusion criteria are chosen much broader since hybrid procedures, such as a reconstruction of the common femoral artery, are allowed. Moreover, the anti-platelet regime and the use of statins are standardized. The wide inclusion criteria are chosen because they mimic common surgical practice and thereby they reduce the risk on inclusion problems as was the case in the Scandinavian trial [16].

With the introduction of the heparin-bonded technology in the endograft the design of the stent has also been changed. The proximal edge of the endograft has no longer a straight, but a contoured edge (Figure 1). This adaptation will reduce infolding in case of oversizing, thereby maintaining laminar blood flow and preventing intimal hyperplasia and thus edges stenosis. The expected effect of the new endograft may therefore not only be attributed heparin-bonding technology.

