**Methods/design:**

Two-hundred-twenty-two patients with peripheral arterial occlusive disease, category 3-6 according to Rutherford, will be randomized in two treatment arms; 1. the surgical femoro-popliteal bypass, venous whenever possible, and 2. the heparin-bonded endoluminal bypass. The power analysis was based on a non-inferiority principle, with an effect size of 90% and 10% margins (alpha 5%, power 80%). Patients will be recruited from 5 teaching hospitals in the Netherlands during a 2-year period. The primary endpoint is primary patency and quality of life evaluated by the RAND-36 questionnaire and the Walking Impairment Questionnaire. Secondary endpoints include secondary patency, freedom-from-TLR and complications.

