## Methods and design

### Study design

The design of the study is a multicentre prospective randomized controlled trial comparing the patency of the heparin-bonded endograft to the venous surgical bypass. Endpoints are primary patency after 1, 2 and 5 years, complications and quality of life.

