### Sample size calculation

The assumption has been made that the heparin-bonded endoluminal bypass will have a similar cumulative primary patency at one year compared to the venous bypass. For a non-inferiority trial with an effect size of 90% and a margin of 10%, 111 patients per group are needed (alpha 5%, power 80%). The effect size of 90% refers to an estimated patency rate at one year in the surgical control arm.

The assumption has been made that the heparin-bonded endoluminal bypass will have an increase in QOL, as measured by a 10-point increase in the SF-36 score, at 30 days follow-up. With a standard deviation of 20, 63 patients per group are needed (alpha 5%, power 80%).

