### Open surgical technique

The surgical femoropopliteal bypass is performed according to local protocols. Preferably the greater saphenous vein is used as conduit in all patients. The used vein has a diameter of at least 3.5 mm. Pre-operative vein mapping may be performed, but is not obligatory. When the great saphenous vein is unavailable or unsuitable a prosthetic graft may be used. When a prosthetic conduit is used the participating surgeon will explicit this choice. All patients will be included in the intention-to-treat analysis.

Post procedurally, all patients will be treated with acetylsalicylic acid 80 mg and clopidogrel 75 mg for the first year unless oral anticoagulation is indicated for other reasons. After 1 year patients may be switched to one thrombocyt aggregation inhibitor. All patients receive statin treatment, started before the intervention.

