### Statistical analyses

Data concerning the 1, 2, and 5 year follow-up will be analyzed for both study groups on an intention-to-treat and a per-protocol manner by student t-test (normal distribution) of Mann Whitney U-test (skewed distribution). Corrections will be made for study centre. Additionally, in case of sufficient numbers, the data will be analyzed for different TASC II categories; otherwise the analyses will be additionally adjusted for TASC II categories. Patency rates will be presented as Kaplan Meier curves including censoring.

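### The aim is stated against the venous bypass, but the randomised comparator is a vein-preferred surgical arm with prosthetic grafts allowed, so intention-to-treat cannot by itself support non-inferiority to vein

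*Protocol article*

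**What the plan says.** The article names two different comparators.

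- **Venous bypass.** The Abstract's Background paragraph, Study objectives and the first aim in the Discussion all name it. Study design speaks of "comparing the patency of the heparin-bonded endograft to the venous surgical bypass".
- **Surgical bypass, whatever the conduit.** The Abstract's Methods/design paragraph defines the control arm as "the surgical femoro-popliteal bypass, venous whenever possible". The Abstract's Discussion paragraph and the closing paragraphs of the main Discussion also speak of surgical bypass.

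Sample size calculation uses both. It assumes similarity to the venous bypass and then says: "The effect size of 90% refers to an estimated patency rate at one year in the surgical control arm".

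Open surgical technique lets the surgeon use a prosthetic graft when the saphenous vein is unavailable or unsuitable, and keeps all patients in ITT. It adds: "Pre-operative vein mapping may be performed, but is not obligatory". Vein suitability may therefore be unknown at randomisation.

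The analysis is planned "on an intention-to-treat and a per-protocol manner". The Discussion says ITT serves to compare with usual surgical practice, where "some patients will not have a vein usable for the bypass and that some endoluminal procedures will be converted to open surgery". It says the per-protocol analysis informs on the endoluminal bypass itself.

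**The concern.** A non-inferiority conclusion is only as strong as the comparator behind it. By the article's own figures a prosthetic bypass has lower one-year patency than vein. Each prosthetic graft in the surgical arm therefore lowers the rate that the endograft has to approach. If the result is then worded as non-inferiority to the venous bypass, which the article calls the gold standard, the claim goes beyond what the randomised comparison tested. An endograft that is 10 points or more worse than vein would pass more often than the stated alpha suggests.

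**Working it through.** **Inputs from the article**

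- Sample size calculation: 90% one-year patency in the surgical arm, 10-point margin, alpha 5% (sidedness not stated), 80% power, 111 per group.
- Background: one-year primary patency 87% for vein. For the trial of covered stent against prosthetic bypass, 73% and 74%, read in that order.

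**Input assumed:** the prosthetic share f in the surgical arm. The article gives none.

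**1. The plan's own figure.** With 90% in both arms:

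n = (z_alpha + z_beta)² × 2 × 0.90 × 0.10 / 0.10²

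- One-sided 5%: (1.645 + 0.842)² × 0.18 / 0.01 = 111.3, which matches 111.
- One-sided 2.5%: 141.3, which does not.

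So the 5% was used one-sided, and that level is taken as nominal below.

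**2. The effective margin against vein.** The ITT control rate is

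pS = 0.87(1 − f) + 0.74f = 0.87 − 0.13f

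The test asks whether pE − pS > −0.10. Substituting pS, this is pE − 0.87 > −(0.10 + 0.13f). Against vein the margin is therefore 10 + 13f points.

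**3. Chance of a false claim against vein.** Put the endograft exactly at the margin below vein, pE = 0.77, with no conversions and 111 per arm:

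SE = √[pS(1 − pS)/111 + pE(1 − pE)/111]

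P(claim) = Φ((pE − pS + 0.10)/SE − 1.645)

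For f = 20%: pS = 0.844, SE = 0.0527, (0.77 − 0.844 + 0.10)/0.0527 = 0.493, and Φ(0.493 − 1.645) = 12.5%.

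| Prosthetic share f (assumed) | ITT control rate | Effective margin v vein | P(claim) |
|---|---|---|---|
| 0% | 87.0% | 10.0 points | 5.0% |
| 5% | 86.4% | 10.7 points | 6.4% |
| 10% | 85.7% | 11.3 points | 8.2% |
| 20% | 84.4% | 12.6 points | 12.5% |
| 30% | 83.1% | 13.9 points | 18.0% |

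**4. Sensitivity, at f = 10%, 20%, 30%**

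- Vein at the planning rate of 90%, endograft 80%, prosthetic 74%: 9.4%, 15.8%, 24.2%.
- Smaller conduit gap (vein 90%, endograft 80%, prosthetic assumed 80%): 7.5%, 10.8%, 14.9%.
- Step 3 inputs tested at one-sided 2.5%: 4.4%, 7.1%, 10.9%, against a nominal 2.5%.

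The direction is the same throughout. The size depends on f and on the gap between vein and prosthetic patency.

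**The case against.** **The target of ITT is disclosed.** The Discussion says ITT compares with usual surgical practice, the Abstract defines the control arm as vein-preferred, and the 90% refers to the surgical arm. Against that comparator prosthetic use inflates nothing, because the mixed arm is the comparator. This stands. The percentages above are error rates only for a claim about vein, so the fault lies in the stated aim and not in the ITT analysis.

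**Both ITT and per-protocol analyses are planned, and nothing makes ITT alone decisive.** This also stands. A reader might infer that the trial has no rule on which analysis decides. The article does not show that: such a rule, and the definition of the per-protocol set, may be in the full protocol or analysis plan.

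**The inputs are soft.** The share f is assumed, vein is preferred in all patients, and the 87% and 74% are not shown to come from comparable populations. This limits the size. It does not remove the mismatch, which is in the text.

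**A reader might infer that conversions to open surgery dilute the contrast from the other side.** The documents do not support that. The definition of primary patency does not say how a conversion is scored. With vein 87%, endograft 77% and no prosthetic grafts, 5% or 10% conversions raise the false-claim rate from 5.0% to 6.1% or 7.4% if a converted patient counts at the vein rate. If conversion counts as loss of patency, the rate falls to 0.9% or 0.1%. The effect is small in one direction and reverses in the other.

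**Conclusion.** The point holds as a mismatch between the stated aim and the comparator randomised. The ITT analysis can support non-inferiority to surgical bypass with vein preferred. It cannot alone support non-inferiority to the venous bypass.

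On the article's 87% and 74%, the effective margin against vein is 10 + 13f points. The chance of a false vein claim at the margin is about 8%, 12.5% or 18% for f = 10%, 20% or 30%, against a nominal one-sided 5%. For scale, the earlier covered stent at 73% lies 14 points below vein, and at f = 30% the effective margin is 13.9 points. These figures rest on the assumed f, on the two literature rates applying to this population, and on 111 evaluable patients per arm.

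A reader might go further and require agreement with a per-protocol set limited to vein grafts and completed endografts before any non-inferiority conclusion. That does not follow. Prosthetic grafts are permitted, so using one is not a protocol deviation. Removing those patients selects on conduit in one arm only. Because vein mapping is optional, matching endograft patients cannot be reliably identified, so the comparison is no longer randomised. It would also cost power: with endograft and vein both at 90%, prosthetic 74%, f of 20% to 30% and conversions of 0% to 10%, simulation puts the chance that both analyses succeed at about 72% to 77%, below the planned 80%.

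**What to change.** 1. Name one comparator throughout: the Abstract's Background paragraph, Study design, Study objectives, Sample size calculation and the first aim in the Discussion. The comparator randomised is "the surgical femoro-popliteal bypass, venous whenever possible".
2. Word the ITT non-inferiority conclusion against that comparator, and make no claim of non-inferiority to the venous bypass from ITT alone.
3. Report the comparison with vein-grafted patients as a supportive, non-randomised analysis, and show the share of prosthetic grafts in the surgical arm beside it.

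This needs no extra patients and no change to the primary analysis. The cost is a narrower headline claim.
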